### Monitoring and Evaluation

#### Community Assessment

The community-level assessment data will be collected through the annual Mayo Clinic Comprehensive Cancer Center Community Cancer-focused Needs Assessment. The Mayo Clinic conducts an annual needs assessment that captures the following variables in the Cancer Center catchment areas, which include both study counties: demographics, health status, health care access, information seeking, and health information access, engagement with Cancer Center, cancer history (personal and family), health behaviors, community attributes, mental health/wellbeing, and clinical trials participation. Participants within the study counties will be purposefully oversampled during the study period. Focusing on the following variables, we will compare the study counties controlling for demographic variables: health status, health care access, information seeking and health information access, cancer history, health behaviors, and clinical trials participation. First, the data will be summarized using standard descriptive statistics for demographic and outcome variables. Subsequently, comparisons of the intervention county (Duval and St. Johns) and the comparative county (Volusia) on study variables will be conducted to assess the similarity of the groups using appropriate tests, such as the *t* test, Wilcoxon test, or chi-square test, and 95% CIs.

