**Conclusions:**

We successfully co-designed the CoLLab REACH services at 3 ALPs. Using a longitudinal pretest-posttest design, we will assess the intervention’s impact at both the individual and community levels to evaluate the feasibility of this community-based, culturally informed approach. In addition, we will examine the feasibility of replicating the CoLLab Learning Health System in underserved communities nationwide.

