A notable aspect of the CoLLab study is its use of a precision community health framework. Precision community health involves tailoring health interventions to specific communities, considering social, cultural, behavioral, and environmental contexts [19-21]. The emphasis is on community-level engagement and implementation, rather than just population-level analytics. The key characteristics include (1) use of community-specific data; (2) focus on engaging the community in designing and delivering interventions; (3) interventions that are context-sensitive and community-tailored, not just statistically targeted; and (4) involvement of community-based participatory research.

The primary objective of this study is to assess the feasibility of establishing a CoLLab Learning Health System within 3 American Legion Posts (ALPs) as *“*community connector sites” that can facilitate access to prostate health REACH services for Black men. The American Legion is the nation’s largest wartime veterans service organization aimed at advocating patriotism across the United States through diverse programs. With a mission to enhance the well-being of America’s veterans, their families, military, and communities through devotion to mutual helpfulness, the American Legion has more than 12,000 Posts in communities throughout the United States and over 200 posts in Florida. The specific aims of the study are (1) to cocreate real-life user-centric CoLLab Learning Health System at 3 ALPs; (2) using a pretest-posttest design, evaluate the impact of the System at the individual and community levels; and (3) to explore the feasibility of replicating the CoLLab Learning Health System in Black communities nationally.

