### Study Overview

This study is conducted by members of the iCCaRE Consortium, established in 2022 to address the disproportionate burden of CaP among Black men worldwide through research, research training, community engagement, and outreach (iccareconsortium.org). Four ALPs in Black communities in Florida were selected, with 3 serving as intervention sites (ALPs 197, 244, and 194) and one as a comparative site (ALP 187). The study focuses on the final 3 steps of the Intervention Planning Framework:

Step 3: Program Design – Translating strategies into operational plans, including materials development, design, pretesting, and production.Step 4: Adoption and Implementation Plan – Establishing procedures and structures to support intervention delivery.Step 5: Monitoring and Evaluation Plan – Developing processes for ongoing assessment of implementation fidelity, outcomes, and impact.

The study design is a 30-month, mixed methods, pragmatic clinical trial to evaluate the feasibility, effectiveness, and scalability of this community-based intervention.

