### Research Intervention and Comparator Sites

The research setting is ALPs in Northeast Florida. The Posts selected for this IDEA award are highly active in their communities, located in underserved minority neighborhoods, and primarily have minority veteran members. The CoLLab sites included one Hub in Duval County (Post 197) and 2 Spokes, Posts 244 in Duval County and 194 in St. Johns County. The comparative site was Post 184 in Delan County.

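### Aim 2 promises a pretest-posttest evaluation of community impact, but the community analysis written out compares counties for similarity, with no before-after contrast and with example tests that cannot make the promised adjustment

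*Protocol article*

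**What the plan says.** The second specific aim (Protocol article, Introduction) is, "using a pretest-posttest design, evaluate the impact of the System at the individual and community levels". The Abstract's Conclusions repeat it: "Using a longitudinal pretest-posttest design, we will assess the intervention’s impact at both the individual and community levels".

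The community analysis appears under Methods, Monitoring and Evaluation, Community Assessment:

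- Data source: "The community-level assessment data will be collected through the annual Mayo Clinic Comprehensive Cancer Center Community Cancer-focused Needs Assessment".
- Sampling: "Participants within the study counties will be purposefully oversampled during the study period".
- Adjustment: for six groups of variables (health status, health care access, information seeking and access, cancer history, health behaviors, clinical trials participation), "we will compare the study counties controlling for demographic variables".
- Analysis: descriptive statistics first, and then "comparisons of the intervention county (Duval and St. Johns) and the comparative county (Volusia) on study variables will be conducted to assess the similarity". The t, Wilcoxon and chi-square tests are given as examples, with 95% CIs.

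The comparator is labelled in three places. Study Overview has "one as a comparative site (ALP 187"). Research Intervention and Comparator Sites has "The comparative site was Post 184 in Delan County". Community Assessment has Volusia as the comparative county; it also speaks of both study counties and then names three.

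**The concern.** A pretest-posttest evaluation of impact needs a measurement before the intervention, one after it, and a contrast between them, here set against the same contrast in the comparison county. The Community Assessment section describes only a contrast between counties. Its stated purpose, to assess similarity, belongs to a balance check and not to an estimate of effect.

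If the section is followed as it stands, both possible results mislead. A significant difference may only reflect long-standing differences between counties in care access or trial participation. A non-significant one shows neither that the counties are similar nor that the intervention had no effect, because failing to reject is not evidence of equality. The community half of Aim 2 would go unanswered although the survey is run every year.

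The adjustment sentence adds an inconsistency. Control for demographics is promised, yet each example test is a two-sample test that takes no covariates.

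**Working it through.** **1. Aim against analysis.** The article states no sample size, alpha, power or effect size for the community comparison, so there is no figure to reproduce. The main check is of the text.

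| Element | Individual level (Statistical Analyses) | Community level (Community Assessment) |
|---|---|---|
| Similarity comparison by t, Wilcoxon or chi-square | Yes, explicitly at baseline | Yes, timing not given |
| Model for the group difference | Generalized linear mixed models | None named |
| Time-point contrasts | Baseline and months 4, 8, 12 | None |
| Trend over time by group | Yes | None |
| Covariate control | Possible within the models | Promised, no method named |

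The similarity sentence is almost the same in both sections. At the individual level it opens the analysis and impact models follow. At the community level nothing follows it.

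**2. What a single-wave county test does when there is no effect (illustration).** None of these inputs is in the article. Assume item prevalence p1 = 0.40 in one county group and p2 = 0.45 or 0.50 in the other (an existing gap d of 5 or 10 points left after any adjustment), no intervention effect, n independent respondents per group, and a two-sided 5% test.

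With pbar = (p1 + p2)/2, the rejection probability in the dominant tail is

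Phi{ [d − 1.96·sqrt(2·pbar(1 − pbar)/n)] / sqrt[(p1(1 − p1) + p2(1 − p2))/n] }.

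Example, n = 300 and d = 0.10: pbar = 0.45. The critical difference is 1.96 × sqrt(2 × 0.2475/300) = 0.0796. The standard error is sqrt(0.49/300) = 0.0404. Then (0.10 − 0.0796)/0.0404 = 0.505, and Phi(0.505) = 0.693.

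| n per group | Gap 5 points | Gap 10 points |
|---|---|---|
| 100 | 10.6% | 29.4% |
| 300 | 23.5% | 69.3% |
| 500 | 35.9% | 89.0% |

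Every one of these rejections is a county difference that the intervention did not cause. Their frequency rises with n, so oversampling the study counties makes the problem worse.

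**3. The before-after contrast by county.** If the gap is stable, (post − pre in intervention counties) − (post − pre in comparison county) has expected value d − d = 0 at every n. The price is precision. With independent waves of equal size the variance doubles, so the standard error grows by sqrt(2) = 1.41. At n = 300 with a 5-point gap it goes from 0.0403 to 0.0570.

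If the pre-launch wave is smaller, the factor is sqrt(1 + n_post/n_pre). With 300 after and 100 before (assumed), it is sqrt(1 + 3) = 2.0, so the standard error becomes 2.0 × 0.0403 = 0.0806. This matters because oversampling is stated only for the study period.

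**The case against.** The strongest defence is that the similarity sentence nearly repeats the baseline check in Statistical Analyses. It may have the same role here, with the demographics-controlled comparison as the real outcome step. That reading is possible but not secure: the community version drops the reference to baseline and comes as the second step after descriptive statistics. Even if it is granted, the controlled comparison is still between counties, with no before-after element, so the gap between aim and analysis remains.

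It can also be said that a condensed article may leave models and survey waves to the full protocol or SAP. This holds for detail. It does not cover an analysis that the article writes out and that does not match its stated aim.

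Four stronger readings may tempt a reader, and the article does not support them:

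- *The county comparison is unadjusted.* Demographic control is promised and the test list is open. The supportable point is that no named method can deliver it. For the same reason an existing gap does not pass in full into the result; only the part not explained by demographics does.
- *The data cannot show a before-after change.* The survey is annual, so the limit lies in the analysis as written.
- *Oversampling is ignored and the analysis is not limited to Black men aged 30 to 80.* The article is silent on both, and silence is not a decision against them.
- *The effect is too diluted at county level to be seen.* The article gives no county population. The sites are also open to the public (Study Timelines), so enrolled men are not the only ones exposed. No dilution figure can be derived.

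On weight, the primary objective is feasibility and the primary outcomes are individual-level. No primary conclusion rests on the community survey.

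**Conclusion.** The point stands in limited form. Aim 2 and the Abstract promise a pretest-posttest evaluation of community impact, and the only community analysis written out has no before-after contrast. It promises an adjustment that its example tests cannot make. As written, it would confuse stable county differences not explained by demographics with impact.

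The text comparison establishes the mismatch without any numerical assumption. The 11% to 89% range only illustrates its possible size and depends wholly on the assumed prevalence, gap and group sizes.

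This should be corrected, because half of a stated aim has no matching analysis. It does not affect the individual-level outcomes.

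The conflicting comparator labels (Post 187 or 184; Delan County or Volusia; both or three counties) are a separate and secondary matter. They leave unclear which Post and county serve as the comparison and whether the survey covers it.

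**What to change.** 1. Name the survey waves: the last annual wave before the sites opened, and the follow-up waves.
2. Make the impact analysis a linear or logistic regression, according to type, of each listed variable on county group, wave and their interaction, adjusted for named demographic variables. Report the interaction with its 95% CI.
3. Label the result exploratory. With two intervention counties and one comparison county, a county's own trend cannot be separated from the intervention effect.
4. Keep the t, Wilcoxon and chi-square tests for description of the pre-launch wave.
5. If no comparable pre-launch wave exists in all three counties, state that the community comparison is descriptive and cannot show impact, and reword Aim 2 and the Abstract to match.
6. Separately, reconcile the comparator Post and county across Study Overview, Research Intervention and Comparator Sites, and Community Assessment, and the mention of both study counties with the three named.

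Survey weights for the oversampling and an analysis restricted to Black men aged 30 to 80 are optional details.

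The cost is mainly wording, plus use of an earlier wave of a survey already run every year. The article does not show that such a wave, with the same items, exists in all three counties, so this must be checked first. Intervals will be wider: about 1.41 times with equal wave sizes, and more if the wave before oversampling is small.

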#### Additional Program Assessment

Additional program evaluation will include (1) assessing the reach of the CoLLab Health System prostate health REACH services*,* including extent and patterns of use, number of people reached over the period of the intervention, and demographics of people reached; and (2) the number of people who were successfully navigated for SDOH, clinical trials, and health care. The information from both individual-level and community-level assessments will be used to refine the services.

#### Assessment of Program Replication

To assess the feasibility of replicating the CoLLab Learning Health System and its services in Black communities nationally, we will estimate the direct and indirect costs of transplanting the CoLLab Learning Health System at ALPs in marginalized and minoritized communities. Micro-costing (detailed inventory, measurement, and valuation of each separate cost item) will be used to document the following: (1) start-up costs for development, including personnel, equipment, and training program costs; and (2) costs to implement the services. Based on the actual dollars spent from the grant, we will measure direct costs as follows: identifying all resources used and placing a dollar value on the resources (associated costs). The indirect cost associated with the CoLLab Learning Health System will be the cost of any institutional (Mayo Clinic and ALP) funding and resources used to support the program.

We will also explore the feasibility of transplanting the CoLLab Learning Health System and its services in Black communities nationally through formative interviews and documentation of costs associated with the program. Our ultimate goal is to successfully replicate the CoLLab Learning Health System and its prostate health REACH services. Establishing the process for replication is an exploratory aim and will provide us with feedback on the optimal approach for its implementation in Black communities nationwide. Using formative interviews of the experiences of key personnel and users, investigators will work with the program CAB, CHWs, and early adopters to address the following issues: “Why did the program work, or not work?” “Should program changes or improvements be made to increase the likelihood of success or to address changes in the services or problem situations?” “Were lessons learned that could help make future programs more successful?” and “What other ways can the services be presented? Are there other ways that the services can be promoted and progress tracked?*”* The responses obtained will be developed into a preliminary report: *“*Implementation of the CoLLab Learning Health System in Black Communities.”

### Ethical Considerations

This study will be conducted according to the Declaration of Helsinki. This study received ethical approval from the Mayo Clinic Institutional Review Board (IRB ID: 23‐007988) on August 20, 2024. It was subsequently reviewed by the US Army Medical Research and Development Command (USAMRDC), Office of Human and Animal Research Oversight (OHARO), and Office of Human Research Oversight (OHRO). On September 25, 2024, the USAMRDC OHARO OHRO approved it as a minimal risk study for the enrollment of a maximum of 250 participants. All eligible participants will provide written informed consent prior to being enrolled in this pragmatic trial, and all participants will receive an incentive according to the provisions in the IRB-approved protocol. Only deidentified data of participants will be used for analysis and evaluation to ensure the confidentiality of participants’ information.

## Results

### Engagement With Community Advisory Board

The study commenced after IRB approval, with the nomination of 7 CAB members at each site, with a total of 21 CAB members. The CABs at each intervention site recommended the prostate health REACH services adopted.

### Interventions and Site Activation

Multiple REACH services and programs were available to be adopted at each site based on the needs of Black men. Examples include the following:

The iCCaRE Consortium SDOH Navigation Services, which was modeled after the American Academy of Family Physicians EveryONE Neighborhood Navigator, provides navigation for community members for food, housing, transportation, employment aid, legal aid, and financial support within or near the zip code.The Wellness RX program was implemented to address some health needs of the communities around the posts. The wellness program includes wellness events, interactive demonstrations, such as cooking and exercising, and grocery distribution to address food deserts.The Prostate Health Support group is a monthly support group led by CaP survivors and interested participants within the community. Issues around prostate health are discussed with emphasis on the need for screening, early diagnosis, and the pathway to survivorship.The Educational resources and videos on Prostate Cancer [38] are educational videos, with the setting in a barbershop, that educate Black men on CaP prevention, screening, detection, treatment, survivorship, and advocacy, and other resources to be shared with the participants.The CaP Advocacy training program was also developed to train cancer survivors and advocates to engage their communities, develop, and implement cancer health and survivorship programs.

### Training of CHWs for Delivery of Intervention

Before the activation of the above intervention, CHWs were trained to be able to deliver CoLLab prostate health REACH services and navigation from January to March 2024. Their involvement is essential to the success of the CoLLab Learning Health System. Two phases of paid training were developed to prepare CHWs for their roles.

The first phase, General Training, was facilitated by a certified CHW trainer from one of our community partner organizations. Using an approved curriculum from the Florida CHW Certification Board, she provided 30 hours of instruction and supported trainees in preparing for the CHW certification examination. Following completion of the required curriculum, she continued to offer updates and continuing education in alignment with Florida CHW certification requirements.

The second phase, Prostate Health REACH Services Training, was delivered by members of the research team and included both didactic instruction and supervised practice in April 2024. Study team members engaged in role-play as early adopters to support skill development. A nongraded quiz followed each didactic module to assess comprehension, and results were shared with trainees to promptly address any areas of confusion. CHWs also conducted a 30-minute “mock intervention” with a team member. These sessions were audio- and video-recorded for review by the training team, who used the recordings to provide feedback and strengthen CHW competencies.

The third phase of CHW capacity building includes continuous training and retraining scheduled throughout the study period. The first was the CHW retreat held in January 2025, and the second was held in January 2026. We anticipate holding another retreat by September 2026.

### Data Collection

Data collection commenced in October 2024. Baseline recruitment for the intervention arm has been completed, with 195 Black men enrolled across intervention ALPs. To date, 11 participants have been enrolled at the control ALP, and recruitment for the control arm remains ongoing. Once data analyses are completed, the results will be shared scientifically through scientific conferences and publications. In addition, community reports will be developed and disseminated publicly.

## Discussion

### Principal Findings

The CoLLab study addresses a longstanding and well-documented public health challenge of the disproportionate burden of CaP among Black men as well as the persistent structural, interpersonal, behavioral, and systemic barriers that shape their cancer care experiences [3]. Despite decades of research, Black men continue to face inequities across the CaP continuum, driven by multilevel determinants spanning health-system factors, provider-level dynamics, and individual-level constraints. The CoLLab Learning Health System model represents an innovative, community-driven strategy to intervene at multiple levels simultaneously by integrating real-time learning, cocreation, trusted CHWs, and culturally grounded REACH services into community environments where Black men already gather.

The use of a precision community health framework strengthens the contextual relevance of this intervention. Precision community health approaches emphasize designing interventions based on localized cultural, behavioral, environmental, and social contexts rather than population-level generalizations [6,28]. By grounding CoLLab activities in community-derived data—through CAB input, focus groups, interviews, and existing needs assessments—this study ensures that intervention components align with the lived experiences and priorities of Black men in Northeast Florida. This approach increases cultural congruence, fosters sustained engagement, and supports the development of long-term community infrastructures for prostate health promotion.

A major strength of the CoLLab model is its integration of CHWs as frontline navigators and educators, a strategy supported by extensive evidence showing that CHWs improve cancer knowledge, navigation, and outcomes among underserved populations [7-9]. Their trusted role within communities enhances communication effectiveness, increases service uptake, and mitigates historical mistrust of health systems. The 2-phase training program equips CHWs with both general competencies and prostate-specific content, ensuring they can deliver tailored education and support across the CaP continuum. Their involvement also aligns with core CoLLab Learning Health System features, including continuous learning, rapid feedback integration, and real-time quality improvement [6].

The digital divide poses an additional challenge to achieving cancer care equity for Black men. Prior research shows that although they use mobile devices at high rates, gaps in broadband access, digital literacy, and trust in digital health tools persist and contribute to inequity in cancer screening, communication, and clinical trial participation [15-17]. By embedding digital tools—including internet access points, evidence-based educational media, and culturally adapted technologies such as ViRA—within community-based CoLLab sites, this study provides a mechanism to introduce digital health resources in a supportive environment. This strategy may help reduce technology-related barriers documented in the literature, including usability challenges, unfamiliarity with digital interfaces, and cultural perceptions that digital interactions lack credibility compared with face-to-face communication [16-18].

The design of this study enhances real-world relevance and supports exploration of both implementation feasibility and preliminary impact. Mixed methods evaluation, integration of a comparison site, and systematic tracking of service utilization allow for a nuanced understanding of how CoLLab functions within community settings. This approach is consistent with emerging literature on community-engaged, context-adapted cancer control interventions, which highlight the importance of iterative feedback, cocreation, and flexible implementation strategies in achieving population-level impact [10,11].

The CoLLab study also lays essential groundwork for future replication and scalability. Micro-costing methods and formative interviews with CHWs, CAB members, and early adopters will yield practical insights into what is required to transplant this model into other Black communities. Literature on Living Labs and community-centered health innovation emphasizes the importance of understanding implementation context, resource demands, and user-experience data to support broad dissemination [4,5,28]. Findings from this study will help inform future implementation science research evaluating real-world effectiveness and long-term sustainability.

